### Study outcomes

Primary outcomes will be major adverse cardiovascular events (MACE), defined as composite of cardiovascular death, myocardial infarction, cerebral infarction, hospitalization because of heart failure or unstable angina pectoris; all-cause mortality and annually medical economic costs in 2 years.

Secondary outcomes will include: ①Mean HGB changes from baseline to the 16th week and percentage of patients within HGB treatment target (110–130 g/L). ②Changes from baseline and variations in the mean HGB level throughout the whole study periods (up to 108 weeks). ③Changes of serum iron metabolism indexes (Hepcidin, ferritin, transferrin, transferrin saturation, and total iron binding capacity) as well as requirements for intravenous iron replacement from baseline to the end of the study(up to 108 weeks). ④Changes of blood pressure and antihypertensive medications from baseline to 16th week. ⑤Changes of serum lipids profile from baseline to 16th week. ⑥Changes of the following laboratory results (collected in the Sichuan provincial dialysis registration system) from baseline to the end of study, dialysis related parameters, dialysis adequacy and chronic kidney disease- mineral bone disorder (CKD-MBD) markers (serum phosphorus, calcium, and parathyroid hormone). ⑦Mean weekly dosage of Roxadustat to maintain HGB within the treatment target. ⑧Adverse events (AE) during the follow-up period, with a focus on drug discontinuation due to AE. ⑨Annual economic cost related to hospitalization, outpatient treatments, medical insurance coverage and out-of-pocket payments.

### Data collection

The de-identified data were collected in REACH via Research electronic data capture (REDCap [14, 15], hosted at Sichuan Provincial People’s Hospital) pre-designed forms from baseline to week 108/2 years. The table with an identification code will be kept within the study site in a secure way. The provision of de-identified medical records will be required for judication for the MACE outcome. Participants will be followed up to 2 years except that they withdraw from the study, have their dialysis type changed, receive kidney transplantation or have lost follow up.

Dialysis data from each study site in the provincial dialysis registry will be collected via a dialysis software provided by the Sichuan Quality Control Center of Renal Disease at the end of the first and second study year.

A questionnaire focusing on medical expense for the participants will be collected at the end of the first and second year of the study.

The target sample size of the ROAD participant is greater than 250 basing on the MACE incidence of at least 20% [16, 17] within 2 years among ROAD and dialysis registry cohort, basing on noninferiority assumption with a marginal difference of 0.02 (10% of MACE incidence), actual difference of -0.08 (40% of MACE incidence),α = 0.05 and 1-β = 0.8, allowing a drop rate of 15%, using ‘Non-Inferiority Tests for the Difference Between Two Proportions’ of PASS software 15.0.5.

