### Study population

The participants included in the ROAD study will be patients with renal anemia in the context of end-stage kidney disease on dialysis (both hemodialysis and peritoneal dialysis), and on Roxadustat treatment who consent to the study. The de-identified data from the provincial dialysis registry of dialysis patients with renal anemia will be serves as a control group. The study was approved by the Institutional Review Board at Sichuan Provincial People’s Hospital (2019 − 196). The informed consent obtained from study participants will be written.

Inclusion criteria include:①Age 18–90 years; ②End-stage kidney disease patients who are receiving maintenance hemodialysis or peritoneal dialysis;③Dry weight 45–160 kg; ④Renal anemia, defined as HGB < 130 g/(male), HGB < 120 g/L(female) or HGB is maintained normal by ESA; ⑤willing to participate in the study with informed consent. Exclusion criteria includes:①patients with pre-existing malignancy; ②Known history of hematological disorders including myelodysplastic syndrome, multiple myeloma, hereditary hematologic disease such as thalassemia, sickle cell anemia, pure red cell aplasia, or other known causes for anemia other than CKD or dialysis. ③Patients who cannot complete the follow-up study.

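### Primary-outcome follow-up ends when a ROAD participant withdraws or is lost, but no matching rule is given for the registry controls, so the two groups are followed under different rules

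*Protocol article*

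**What the plan says.** All places are in the Methods/Design part of the protocol article.

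- **Study outcomes.** MACE and all-cause mortality over 2 years are primary outcomes.
- **Data collection, follow-up rule.** "Participants will be followed up to 2 years except that they withdraw from the study, have their dialysis type changed, receive kidney transplantation or have" been lost to follow-up, which is the fourth exit in that sentence. The word used is participants, which the Study population section applies to the ROAD cohort.
- **Study population.** ROAD patients are those "on Roxadustat treatment who consent to the study". For the comparison group: "The de-identified data from the provincial dialysis registry of dialysis patients with renal anemia will be serves as a control group". No consent, withdrawal or stopping rule is described for it.
- **Data collection, registry.** "Dialysis data from each study site in the provincial dialysis registry will be collected via a dialysis software", at the end of study years 1 and 2. A table with an identification code stays at each site.
- **Study outcomes, item 6.** Some secondary laboratory outcomes are "collected in the Sichuan provincial dialysis registration system", which implies that ROAD patients also appear in the registry.
- **Data collection, sample size.** More than 250 ROAD participants, "allowing a drop rate of 15"%, with a non-inferiority margin of 0.02 on a 2-year MACE incidence of at least 20%.
- **Data analysis.** The primary comparison is by Cox regression, with a propensity score method as a sensitivity analysis.

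**The concern.** A participant who withdraws or is lost is no longer observed for MACE or death. Only a consented cohort can withdraw consent, so this exit exists on the ROAD side alone. The controls are seen through an extraction that does not depend on their agreement to continue.

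If people leave because they are ill or because their care has moved, their later event rate may exceed that of the people who stay. Censoring them in one group then lowers that group's estimated MACE and mortality, pulls the hazard ratio towards Roxadustat, and moves a non-inferiority comparison towards success. Adjustment for measured baseline differences, by Cox covariates or a propensity score, does not by itself correct for this.

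The point is limited to study withdrawal and loss to follow-up. It does not turn on change of dialysis type or transplantation.

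**Working it through.** **1. The plan's own figure.** Control risk is 0.20. The assumed difference of -0.08 gives 0.12 in ROAD, so the distance to the margin is 0.02 + 0.08 = 0.10. With equal groups and one-sided 0.025 (neither is stated):

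n = (1.960 + 0.842)² × (0.20×0.80 + 0.12×0.88) / 0.10² = 7.849 × 0.2656 / 0.01 ≈ 208.5, so 209 per group, and 209 / 0.85 ≈ 246.

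A pooled variance gives 211, then 249. The Farrington-Manning method gives 212, then 250. The target of more than 250 is therefore reproduced, and the 15% enters only as the divisor 0.85. The calculation does not split it by group or by reason for leaving.

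**2. Model for the effect of leaving.** From the documents: 2-year MACE 20%, drop allowance 15%, 250 ROAD participants, margin 2 points. Assumed: constant hazards, true risk 20% in both groups, controls fully observed, and an event hazard k times higher after leaving. The values k = 1.5 to 3 are illustrative and have no source in the article.

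- Leaving hazard: d = -ln(1 - p)/2 per year. For p = 0.15, d = 0.0813. For p = 0.075, d = 0.0390.
- Let h be the event hazard before leaving and a = h + d - kh. The true 2-year event-free probability is S = exp(-2(h + d)) + d·exp(-2kh)·(1 - exp(-2a))/a. Solve for h so that S = 0.80.
- Estimate with leavers censored: 1 - exp(-2h).
- Approximate hazard ratio against controls: ln(1 - estimate)/ln(0.80).

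Example, p = 0.15 and k = 3: h = 0.0981 and a = -0.1149. Then S = 0.6985 + 0.0813 × 0.5551 × 2.249 = 0.800. The estimate is 1 - exp(-0.1962) = 0.178, and the hazard ratio is 0.1962/0.2231 = 0.88.

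| k | All of the 15% is ROAD withdrawal or loss: estimate, bias, HR | Half of it (7.5%): estimate, bias, HR |
|---|---|---|
| 1 | 20.0%, 0, 1.00 | 20.0%, 0, 1.00 |
| 1.5 | 19.4%, -0.6, 0.96 | 19.7%, -0.3, 0.98 |
| 2 | 18.8%, -1.2, 0.93 | 19.4%, -0.6, 0.97 |
| 3 | 17.8%, -2.2, 0.88 | 18.9%, -1.1, 0.94 |

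Bias is in percentage points; the true hazard ratio is 1.00 throughout.

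**3. Second parameterisation.** Hold the risk before leaving at 20% and let the true ROAD risk rise. With p = 0.15 the true risk is 20.7%, 21.3% or 22.4% for k = 1.5, 2 or 3, while the censored estimate stays at 20.0%. The gap is 0.7 to 2.4 points, and the ROAD rate is understated by a factor of about 0.97 to 0.89. The order of magnitude is the same.

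**4. In patients.** With p = 0.15, between 3.7 events (k = 1) and 8.8 events (k = 3) per 250 fall after leaving and go unseen. The margin corresponds to 0.02 × 250 = 5 patients. At k = 1 the unseen events cost precision but do not bias the Cox comparison.

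**The case against.** Several stronger readings are tempting, and the article does not support them.

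- **That 15% of ROAD is expected to withdraw or be lost.** The figure is a sample-size allowance. Four exits are listed and the 15% is not divided among them. This stands, which is why the half-allowance column is shown; there the bias stays below the 2-point margin throughout.
- **That events are lost mainly from the Roxadustat side.** Registry patients can also transfer or disappear, and the article does not say how their MACE is found or how complete their follow-up is. Similar loss with similar risk would remove the difference; worse capture among controls would reverse it. This stands against any firm statement of direction.
- **That missing events bias the result whatever the reason for leaving.** Counting leavers as event-free in a crude proportion would give -1.5 points even at equal risk (18.5% against 20.0%). The planned analysis is Cox regression, which censors them and has no bias at equal risk. Further missing-data rules may sit in an analysis plan that is not shown.
- **That the registry is deliberately left unused for leavers.** It is named as a study data source, and the article does not say that registry deaths or events will be ignored for them. It is silent.
- **That stopping Roxadustat ends follow-up.** Drug discontinuation is not among the listed exits.

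It is also fair to say that the registry is shown to hold dialysis and laboratory data rather than MACE, and that a patient who leaves a site may leave that site's extraction too.

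What survives all this is the stated rule. It truncates two primary outcomes in one group on grounds that include one the other group cannot meet, and no parallel rule is given for the controls.

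**Conclusion.** The concern holds in a limited form. As written, ROAD participants and registry controls are followed for MACE and death under different rules. The comparison is biased only if leaving is related to risk and loss differs between the groups. The bias is then likely, but not certain, to favour Roxadustat.

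Under the assumptions set out above, the ROAD risk is understated by 0.6 to 2.2 points if the full allowance applies, and by 0.3 to 1.1 points if half does. Only the most adverse combination (the whole 15%, a tripled event rate and fully observed controls) exceeds the 2-point margin. This is a worthwhile and inexpensive improvement, not a demonstrated failure of the study.

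**What to change.** 1. Amend the follow-up rule in the Data collection section so that ending study visits or REDCap contact does not end outcome follow-up for MACE and all-cause mortality.
2. For these patients, take vital status and MACE-related events to 2 years from the year-1 and year-2 registry extraction that observes the controls, linked through the identification code held at the site, unless consent to data use is withdrawn.
3. State one set of censoring rules and one event source, and apply both to ROAD participants and registry controls alike.
4. Add a sensitivity analysis in which ROAD participants who remain unobserved have 1.5 to 3 times the event rate of those followed.

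**Cost.** A change of wording in the protocol and consent form, linkage of at most about 38 patients (0.15 × 250 = 37.5, if the whole allowance applies), and one extra analysis. The consent wording has to permit linkage, so the change is best made prospectively. Registry outcomes may be less detailed than REDCap records, and patients who leave a participating site may still be missed.

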### Data analysis

The comparison in primary outcomes between the ROAD cohort and the registry data will be performed using Multiple Cox regression of risk factors and propensity score method will also be applied as a sensitivity analysis. The medical economic costs will be compared between ROAD cohort and registry control group using the whole population as well as populations stratified by hospital levels, regions, comorbidities.

The efficacy on HGB of Roxadustat in the treatment of anemia of the whole cohort as well as the pre-defined subgroups (including patients with evidence of erythropoietin resistance, patients with chronic inflammation, patients with impaired iron metabolism, and patients on hemodialysis or peritoneal dialysis) will be analyzed in intention-to-treat and per-protocol ROAD population. Treatment heterogeneity will be tested by adding an interaction term to the statistical models.

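### Follow-up ends when the dialysis type changes, although the patient stays in the target population; if the change is related to prognosis, MACE and mortality are informatively censored

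*Protocol article*

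**What the plan says.** The Data collection section of the protocol article sets the end of follow-up: "Participants will be followed up to 2 years except that they withdraw from the study, have their dialysis type changed, receive kidney transplantation"; loss to follow-up is the remaining exception. No reason is given for including a change of dialysis type.

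Other sections bear on this rule:

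- Study population enrols patients with "end-stage kidney disease on dialysis (both hemodialysis and peritoneal dialysis), and on Roxadustat treatment who consent to the study". Both types are eligible.
- The same section defines the comparator: "The de-identified data from the provincial dialysis registry of dialysis patients with renal anemia will be serves as a control group". No restriction by dialysis type is stated.
- Study outcomes makes MACE a primary outcome, along with "all-cause mortality and annually medical economic costs in 2 years".
- Data analysis says that the comparison of primary outcomes with the registry "will be performed using Multiple Cox regression of risk factors and propensity score method will also be applied as a sensitivity analysis". Dialysis type appears there only as a subgroup for the haemoglobin analysis.
- Data collection also describes a second data stream: "Dialysis data from each study site in the provincial dialysis registry will be collected via a dialysis software", at the end of each of the two study years.

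The article does not say whether MACE and deaths after a change of type are still captured, or whether registry controls stop at the same event.

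**The concern.** A transplanted patient leaves dialysis and so leaves the population being studied. A patient who moves between haemodialysis and peritoneal dialysis does not. The rule removes that patient's later time at risk from the two clinical primary outcomes, although the study's stated aim is the long-term effect on them.

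Cox regression needs censoring to be independent of risk, given the covariates in the model. If patients change type because their condition is worsening, the time removed carries a higher hazard. Risk-factor adjustment and propensity scores use information from baseline, so they do not repair censoring driven by what happens after baseline. Nor can a later analysis plan recover outcomes that were never collected.

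At stake is a downward bias in the MACE and death rates of any cohort to which the rule applies, and possibly a biased comparison if it applies to only one.

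**Working it through.** **Inputs from the article (Data collection).** 2-year MACE of at least 20%; non-inferiority margin 0.02; assumed true difference -0.08, which implies 12% in ROAD against 20% in the registry; power 0.80; 15% dropout; target above 250.

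**The plan's own figure.** With 1:1 allocation and one-sided alpha 0.025 (the article gives 0.05 without sidedness):

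n = (1.960 + 0.842)² × (0.12×0.88 + 0.20×0.80) / (0.02 + 0.08)² = 7.849 × 0.2656 / 0.01 = 208.5, so 209.

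209 / 0.85 = 245.9, so 246. The Farrington-Manning form gives 212, and 212 / 0.85 = 249.4, so 250. The target reproduces. The present point does not depend on it; it only supplies the 12% and 20% rates used below.

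**Inputs not in the article (assumed).** Proportion s who switch at month 12 if still event-free: 5% or 10%. Hazard ratio k after the switch: 1, 2 or 3. Hazard before the switch: the same as in non-switchers.

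**Understatement of 2-year risk within one cohort.** Let p be the 2-year risk at constant yearly hazard h = -ln(1-p)/2.

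- True risk = (1-s)(1 - e^(-2h)) + s(1 - e^(-h)·e^(-kh)).
- If switchers are censored at the switch, the remaining data carry only hazard h, so the estimate is 1 - e^(-2h) = p.
- Understatement = s · e^(-h) · [e^(-h) - e^(-kh)].

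At p = 0.12: h = 0.0639, e^(-h) = 0.9381, e^(-2h) = 0.8800, e^(-3h) = 0.8255.

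- k = 2: 0.9381 × 0.0581 = 0.0545
- k = 3: 0.9381 × 0.1126 = 0.1056

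At p = 0.20: h = 0.1116, e^(-h) = 0.8944, e^(-2h) = 0.8000, e^(-3h) = 0.7155.

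- k = 2: 0.8944 × 0.0944 = 0.0844
- k = 3: 0.8944 × 0.1789 = 0.1600

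Multiplying by s gives the understatement in percentage points:

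| 2-year rate | s | k = 1 | k = 2 | k = 3 |
|---|---|---|---|---|
| 12% | 5% | 0 | 0.27 | 0.53 |
| 12% | 10% | 0 | 0.54 | 1.06 |
| 20% | 5% | 0 | 0.42 | 0.80 |
| 20% | 10% | 0 | 0.84 | 1.60 |

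If k is below 1, the sign reverses.

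**Events not observed.** A wider illustration takes 250 participants, switch times uniform over 2 years, s from 2% to 10% and k from 1 to 3. The share of events falling after the switch is s × mean over t of e^(-ht)·[1 - e^(-kh(2-t))]. That is about 0.3-4.1 of 30-33 events at 12%, and 0.5-6.3 of 50-54 events at 20%. These are counts of lost information. They are not the bias of a Cox estimate, because Cox regression allows for the shorter follow-up.

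**The case against.** The strongest reply is that the sentence may govern only the study database. The article also describes registry data from each site at the end of both years, so deaths, and perhaps events, after a switch could be kept by that route. A condensed article may leave such detail to the full protocol. This reply is fair as far as it goes: it is not proven that every later event is lost. But the sentence, as written, ends follow-up, and nothing in the article says outcomes are collected beyond it.

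A second reply is that follow-up limited to the initial modality is defensible, because costs, dialysis parameters, adequacy and weekly dose depend on modality. That stands for modality-dependent outcomes. It is weak for death and MACE, and the article does not offer it as a reason.

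Several stronger readings are tempting, but the article does not support them:

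- *The rule favours Roxadustat.* A reader might infer this because the rule is worded for participants. It requires controls to be followed through a switch, and the article does not say whether they are. If both cohorts stop, the between-cohort bias largely cancels.
- *The bias uses up most of the 0.02 margin.* At a 20% rate the table runs from 0.42/2 = 21% to 1.60/2 = 80% of the margin. At the 12% implied for ROAD it runs from 0.27/2 = 14% to 1.06/2 = 53%. Both ranges assume one-sided censoring, and every switch rate and hazard ratio behind them is assumed.
- *The registry already holds what is needed.* MACE is adjudicated by two doctors from de-identified medical records (Quality control). No section says registry data would support that after a switch. That the registry covers both dialysis types is a fair reading, but it is not stated outright.

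Finally, the 15% dropout allowance may absorb part of the loss of power. It does not remove bias.

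**Conclusion.** The point holds as a stated rule that is badly fixed for two primary outcomes. It ends follow-up for patients who remain in the target population, at an event plausibly tied to prognosis, and the planned baseline adjustment cannot correct for that.

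Its size is uncertain. It rests on assumed switching of 5-10% at month 12 and an assumed two- to threefold hazard afterwards. It would be small with few switches, and absent if the hazard does not change. The within-cohort figures in the table carry over to the ROAD-registry comparison only under one-sided censoring. No direction of bias in that comparison can be claimed from the article. The rule should be amended because the bias is avoidable at low cost, not because it is shown to be large.

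**What to change.** In Data collection, remove change of dialysis type as an end of follow-up for MACE and all-cause mortality. Follow these outcomes to 2 years through any switch. State one end-of-follow-up rule on this point for ROAD and registry patients alike. Keep censoring at the switch as a sensitivity analysis. Modality-dependent secondary outcomes may still stop at the switch, if the text says so.

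The cost is modest. Medical records must still be collected for MACE adjudication in the few patients who switch, and some follow-up will be on a different modality from baseline. No treatment decision changes.

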### Quality control

The investigators will be trained before initiation of the study. A multi-disciplinary team will provide consultation on adjustment of Roxadustat dosage based on HGB level if needed during the study. An online video and handbook will be provided to guide the data entry. The online forms will be provided for data validation to minimized errors with data entry. Data monitoring will be carried out to make sure the accuracy of the data entry. The main outcome of MACE will be judicated independently by two trained doctors using de-identified medical records. A third doctor will be consulted if there are any disagreements. The questionnaire on economic costs will be randomly selected and double-checked with medical insurance department to ensure the authenticity. The data will be locked once the data cleaning completes, and the analysis plan will be prepared and run independently by two statisticians.

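### The between-group MACE comparison is not tied to one event source: adjudicated medical records are described for ROAD, only software-collected registry data for controls

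*Protocol article*

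**What the plan says.** All places are in the protocol article, Methods/Design.

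- **Outcome.** Under Study outcomes, MACE is a "composite of cardiovascular death, myocardial infarction, cerebral infarction, hospitalization because of heart failure or unstable angina pectoris". All-cause mortality and annual medical costs are the other primary outcomes.
- **ROAD data.** Under Data collection, data enter REACH through REDCap "pre-designed forms from baseline to week 108/2 years". The same paragraph adds: "The provision of de-identified medical records will be required for judication for the MACE outcome". It goes on to describe how participants are followed and when follow-up ends.
- **Adjudication.** Under Quality control: "The main outcome of MACE will be judicated independently by two trained doctors using de-identified medical records", with a third doctor for disagreements. The sentence names neither cohort.
- **Controls.** Under Study population: "The de-identified data from the provincial dialysis registry of dialysis patients with renal anemia will be serves as a control group". Under Data collection: "Dialysis data from each study site in the provincial dialysis registry will be collected via a dialysis software", and this happens "at the end of the first and second study year".
- **Comparison.** Under Data analysis: "The comparison in primary outcomes between the ROAD cohort and the registry data will be performed using Multiple Cox regression of risk factors", with a propensity score method as sensitivity analysis.

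**The concern.** The article describes two ways of finding events and then compares the counts. On one side, follow-up forms lead to medical records that two doctors review. On the other, dialysis data are pulled from software once a year. Four of the five MACE components are clinical events other than death, and the fifth needs a cause of death, so the count depends on how actively events are sought and how strictly they are confirmed.

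If the two cohorts are handled differently, the MACE contrast contains a measurement component. Under-capture in the registry would make Roxadustat look worse than it is. Rejection of unconfirmed events in ROAD only would make it look better. Cox adjustment and propensity scores balance measured baseline risk. They do nothing about an outcome recorded differently by group, and a larger sample does not shrink the error. MACE is also the outcome on which the study was sized.

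**Working it through.** **1. What the article gives for each cohort**

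| | ROAD | Registry controls |
|---|---|---|
| Route | REDCap forms, baseline to week 108 | Dialysis software, end of years 1 and 2 |
| Medical records for MACE | Required, in the REDCap paragraph | No route described |
| Two-doctor adjudication | Yes | Neither stated nor excluded |

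The only listing of registry content is secondary outcome 6 (Study outcomes): dialysis parameters, adequacy and mineral-bone markers. It need not be exhaustive. It does indicate that ROAD patients' results are taken from the provincial system, so they appear to be in the registry.

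**2. The plan's own figure**

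Inputs from Data collection: control rate c = 0.20; difference -0.08, so ROAD rate r = 0.12; margin 0.02; alpha 0.05; power 0.80; dropout 15%. Allocation is not stated (1:1 assumed), nor is the sidedness of alpha.

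n per group = (z_alpha + z_power)² × [r(1-r) + c(1-c)] / [0.02 - (r - c)]²

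Reading alpha as two-sided (one-sided 0.025): 7.849 × (0.1056 + 0.1600) / 0.10² = 208.5, so 209; 209/0.85 = 245.9, so 246. The Farrington-Manning score version gives 212, and 250 after dropout. One-sided 0.05 gives 165, and 195 after dropout, which does not match. The target of more than 250 therefore reproduces with alpha read as two-sided.

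**3. Shift from unequal capture**

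The documents give no capture or rejection rates, so these are assumed. With a true 20% in both groups and a relative capture difference d, the spurious difference is 0.20 × d:

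- d = 10%: 0.20 × 0.10 = 0.02, the whole margin.
- d = 20%: 0.20 × 0.20 = 0.04, twice the margin.

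The sign depends on which group loses events. On the ratio scale, closer to the planned Cox model, control capture of 90% or 80% turns a true risk ratio of 1.00 into 1/0.9 = 1.11 or 1/0.8 = 1.25.

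**4. Effect on a test of the planned size**

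With 209 evaluable per group and r, c the observed rates:

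P(non-inferiority) = Φ{ [0.02 - (r - c)] / √([r(1-r) + c(1-c)]/209) - 1.960 }

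*(a) Controls under-captured, ROAD complete, true difference -0.08.* At 90% capture, c = 0.18 and r = 0.12: 0.08/0.0348 = 2.298; 2.298 - 1.960 = 0.338; Φ = 0.63.

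| Control capture | Observed c | Power |
|---|---|---|
| 100% | 0.20 | 80% |
| 90% | 0.18 | 63% |
| 80% | 0.16 | 43% |

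*(b) Adjudication removes ROAD events only, true difference +0.02 (ROAD 0.22).* At 90% retained, r = 0.198 and c = 0.20: 0.022/0.0391 = 0.563; 0.563 - 1.960 = -1.397; Φ = 0.081.

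| ROAD events kept | Observed r | False non-inferiority |
|---|---|---|
| 100% | 0.220 | 2.5% |
| 90% | 0.198 | 8.1% |
| 80% | 0.176 | 21% |

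**5. Dependence on the ROAD rate**

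If ROAD truly runs at the planned 12%, rejecting 10% to 20% of its events removes 0.12 × 0.10 = 0.012 to 0.12 × 0.20 = 0.024, which is 0.6 to 1.2 times the margin. The equivalence of 10% capture with one full margin belongs to a 20% rate in the affected group.

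**The case against.** The strongest reply is that the asymmetry is inferred. The adjudication sentence is not confined to ROAD, and MACE is a primary outcome compared across both cohorts, so the plain wording can cover controls. The sentence on supplying records does not name ROAD either; its position in the REDCap paragraph is what links it to participants. How control events are retrieved may be set out in a full protocol that is not shown. **This part stands.** A reader might infer that controls are unadjudicated, or that the registry holds no MACE events; the article says neither.

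It is also fair that the capture and rejection rates are illustrative, that the two errors act in opposite directions and could partly cancel, that under-capture in controls costs power and does not create a false claim, and that risk-difference arithmetic only approximates a Cox analysis. The study is observational and meant to inform later randomized trials.

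The reply does not remove the point. The article itself fixes both data sources and the direct comparison between them, and control data arrive de-identified with no described path to a medical record. Nor does it help to say that the registry may not hold MACE: if control MACE is to come from the registry, the registry must hold it, and the same count can then be made for ROAD patients. If it does not hold it, records for controls are needed, and their source should be stated.

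**Conclusion.** The point holds conditionally. As described, the event sources for MACE differ between ROAD and the controls, and nothing requires them to be the same for the primary comparison. If ascertainment does differ, the MACE contrast cannot be attributed to Roxadustat, whichever way it falls, and the planned adjustment does not help.

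The size is material against the plan's own margin: a 10% relative difference in capture at a 20% rate equals the full 0.02, and 20% gives 0.04. This rests on assumed capture rates. The power and error figures also assume 1:1 allocation and alpha read as two-sided.

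A reader might go further and conclude that the study will make the drug look harmful, or protective. The documents support neither, since the direction cannot be determined from them. All-cause mortality is less exposed because it needs no event adjudication or cause of death.

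**What to change.** State that the between-group MACE comparison uses the same event source, the same definition and the same follow-up timing in both groups. There are two ways to meet this:

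1. If adjudication of controls is already intended, say so, name the source of their medical records, and apply the same record-based procedure to both cohorts.
2. Otherwise, count MACE in both groups from the registry with one definition. Report adjudicated ROAD MACE descriptively, and use it to estimate how well registry MACE captures true events, for a misclassification sensitivity analysis of the comparison.

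In either case, report all-cause mortality alongside MACE as the endpoint less exposed to this bias. Making it lead the comparative claim would be a preference, not a requirement.

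Cost: option 2 gives a coarser MACE definition for the comparison and needs ROAD participants linked to their registry records. The linkage takes some care, because the data are de-identified and the identification-code table is held at the study site. It also depends on the registry recording the MACE components, which should be confirmed first. Option 1 costs record retrieval and adjudicator time for control events. The choice should be written down before data lock.
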